# PRE-OPerative ECHOcardiograhy for prevention of cardiovascular events after non-cardiac surgery in intermediate- and high-risk patients: protocol for a low-interventional, mixed-cohort prospective study design (PREOP-ECHO)

**DOI:** 10.1186/s13063-022-06701-2

**Published:** 2022-09-14

**Keywords:** Echocardiography, Noncardiac surgery, Trial design

## Abstract

**Background:**

Cardiac evaluation using transthoracic echocardiography before noncardiac surgery is common in real-world practice. However, evidence supporting preoperative echocardiography is lacking. This study aims to evaluate the additional benefit of preoperative echocardiography in predicting postoperative cardiovascular events (CVE) in noncardiac surgery.

**Methods:**

This study is designed as a multicenter, prospective study to assess the utility of preoperative echocardiography in patients undergoing intermediate- or high-risk noncardiac surgery. This trial comprises two studies: (1) a randomized controlled trial (RCT) for patients undergoing intermediate-risk surgery with fewer than three clinical risk factors from the revised cardiac risk index (intermediate-risk group) and (2) a prospective cohort study for patients undergoing intermediate-risk surgery with three or more clinical risk factors, or who undergo high-risk surgery regardless of the number of clinical risk factors (high-risk group). We hypothesize that the use of preoperative echocardiography will reduce postoperative CVEs in patients undergoing intermediate- to high-risk surgery through discovery of and further intervention for unexpected cardiac abnormalities before elective surgery. A total of 2330 and 2184 patients will be enrolled in the two studies. The primary endpoint is a composite of all-cause death; aborted sudden cardiac arrest; type I acute myocardial infarction; clinically diagnosed unstable angina; stress-induced cardiomyopathy; lethal arrhythmia, such as sustained ventricular tachycardia or ventricular fibrillation; and/or newly diagnosed or acutely decompensated heart failure within 30 days after surgery.

**Discussion:**

This study will be the first large-scale prospective study examining the benefit of preoperative echocardiography in predicting postoperative CVE. The PREOP-ECHO trial will help doctors identify patients at risk of postoperative CVE using echocardiography and thereby reduce postoperative CVEs.

**Trial registration:**

The Clinical Research Information Service KCT0006279 for RCT and KCT0006280 for prospective cohort study. Registered on June 21, 2021.

**Supplementary Information:**

The online version contains supplementary material available at 10.1186/s13063-022-06701-2.

## Background

Development of unexpected postoperative adverse events after noncardiac surgery, especially cardiac events, is a major concern to all clinicians including surgeons and anesthesiologists, as well as the patients and their family members. Postoperative cardiovascular events (CVE) are likely to be associated with both patients’ comorbidities and the risk of the operation and anesthesia. Up to 8% of patients experienced cardiovascular death or non-fatal myocardial infarction within 30 days after surgery in a recent prospective study [1]. Although the incidence of all-cause mortality, specifically fatal CVE, after noncardiac surgery has decreased with advanced intraoperative monitoring systems, surgical techniques, and elaborate postoperative management, the frequency of nonfatal CVEs is increasing as surgeries performed in older patients with elevated comorbidity status increase in number [2–6]. Various predictive models have been proposed to assess CVE risk following noncardiac surgery [7–11]. However, previous models only focus on hard outcomes such as fatal and non-fatal myocardial infarction (MI) and cardiac arrest, not on nonfatal but important outcomes, such as unstable angina, stress-induced cardiomyopathy, and acute decompensated heart failure. Therefore, preoperative cardiac risk assessment tools using existing guidelines have limited predictive power for common postoperative CVEs in real-world clinical practice.

Transthoracic echocardiography (TTE) has been widely used to assess the potential risk of postoperative CVE and to detect severe structural heart diseases, such as valvular heart diseases or left ventricular (LV) dysfunction, before noncardiac surgery. Even though TTE is a noninvasive, reproducible, and informative tool for evaluating individual cardiovascular conditions, most guidelines do not recommend preoperative TTE in asymptomatic patients [7, 8, 12, 13]. The benefits of echocardiographic parameters for the prediction of postoperative CVE have not yet been demonstrated in patients without symptoms or signs of cardiovascular disease, and indiscriminate use of preoperative TTE can lead to an unnecessary increase in medical costs. Interestingly, an increasing number of clinicians are using preoperative TTE, not being supported by the current guidelines [7, 8, 12, 13]. Cardiac biomarkers, such as natriuretic peptides and troponins reflecting increased LV wall stress or myocardial injury sensitively, might also have an additive role in the detection of subclinical cardiac diseases and the prognostication for the postoperative CVE [14–18]. However, current guidelines do not recommend the routine use of preoperative biomarkers to predict postoperative CVEs [7, 8, 12, 13].

To bridge this evidence gap, we designed a study entitled “PRE-OPerative ECHOcardiography for the prevention of cardiovascular events after noncardiac surgery in intermediate- and high-risk patients (PREOP-ECHO)”. We hypothesize that preoperative TTE would reduce postoperative CVEs in patients undergoing intermediate- to high-risk surgery by screening and timely addressing hidden cardiac conditions before elective noncardiac surgery. The main purpose of this study is to evaluate the additional benefit of preoperative echocardiography in predicting postoperative CVEs in noncardiac surgery.

## Trial design

### Study objectives

The purpose of this study is to compile data on preoperative TTE from the perspective of reducing postoperative CVEs within 30 days after intermediate- and high-risk noncardiac surgery. Previous risk scoring systems have focused primarily on MI and cardiac arrest as adverse cardiac events [7–11]. Therefore, this trial will encompass all clinically relevant CVEs as primary and secondary endpoints. Further, this trial will develop possible echocardiographic parameters that could be used to determine a preoperative assessment system that would assist in predicting postoperative CVEs. The results from this study will be used to develop Korean guideline for the use of preoperative echocardiography in patients who will undergo noncardiac surgery.

### Study design

Current guidelines do not recommend preoperative TTE in asymptomatic patients undergoing intermediate- or low-risk noncardiac surgery (class of recommendation [COR] III, level of evidence [LOE] C); however, preoperative TTE may be considered in patients who undergo high-risk surgery (COR IIb, LOE C) [8]. Therefore, we will divide participants enrolled in this trial into two study cohorts based on the potential risk of postoperative CVE.

The first study is designed as a randomized controlled trial (RCT) for patients undergoing intermediate-risk surgery who have less than three clinical risk factors from the revised cardiac risk index (intermediate-risk group) (Table 1) [8, 11]. The second study is designed as a prospective cohort study for patients undergoing intermediate-risk surgery who have three or more clinical risk factors or for patients undergoing high-risk surgery regardless of the number of clinical risk factors (high-risk group) (Table 2). We re-classified surgical risk based on the guidelines from the European Society of Cardiology [8] and present specific surgeries in Table 3, including but not limited to the following representative examples. The study designs are shown in Figs. 1 and 2. This trial complied with Standard Protocol Items: Recommendations for Interventional Trials (SPIRIT) guidelines. The SPIRIT checklist can be found in Additional file 1, and the schedule for enrollment, interventions, and assessments is presented in Fig. 3.

**Table 1 Tab1:** Clinical risk factors according to the revised cardiac risk index (Circulation, Lee 1999) [11]

• Ischemic heart disease (angina pectoris and/or previous myocardial infarction^a^) • Heart failure • Stroke or transient ischemic attack • Renal dysfunction (serum creatinine >170 umol/L or 2 mg/dL or a creatinine clearance of <60 mL/min/1.73m^2^) • Diabetes mellitus requiring insulin therapy	

^a^According to the universal definition of myocardial infarction

**Table 2 Tab2:** Inclusion and exclusion criteria for the PREOP-ECHO trial

**Inclusion criteria**	
• Aged 18 to 90 years • Plan to undergo elective non-cardiac surgery	
**Randomized controlled trial** (Intermediate-risk group)	**Prospective cohort study** (high-risk group)
• Intermediate-risk surgery with less than three clinical risk factors	• Intermediate-risk surgery with three or more clinical risk factors or • High-risk surgery regardless of the number of clinical risk factors
**Exclusion criteria**	
• Current symptoms or signs requiring transthoracic echocardiography • Poor functional capacity (< 4 METs) • Life expectancy less than 6 months • Emergent surgery • Low-risk surgery • Participants who underwent TTE within 3 months before study enrollment	

*TTE* transthoracic echocardiography, *MET* metabolic equivalent of task

**Table 3 Tab3:** Detailed examples of intermediate- and high-risk surgery

Intermediate-risk surgery	High-risk surgery
• Hip surgery	• Amputation (except toe/finger)
• Spine surgery (except vertebroplasty)	• Bowel perforation surgery
• Proximal bone surgery (including knee)	• Liver surgery
• Multiple bone fracture surgery	• Bile duct surgery
• Facial bone fracture surgery	• Duodeno-pancreas surgery
• Hollow viscus surgery (stomach, jejunum, colon, rectum)	• Arterial bypass surgery
• Hiatal hernia surgery	• Thoracic endovascular aortic repair
• Distal pancreas surgery	• Open thromboembolectomy
• Splenectomy	• Aorta, major vascular surgery
• Cholecystectomy	• Pneumonectomy
• Hysterectomy	• Lung transplantation
• Exploratory laparotomy	• Esophagectomy
• Nephrectomy	• Total cystectomy
• Kidney transplantation	• Adrenal resection
• Endovascular aortic repair	
• Lung resection	
• Neurosurgery (except transfemoral cerebral angiography)	
• Symptomatic carotid artery surgery	
• Neck surgery (except thyroid/parathyroid)

**Fig. 1 Fig1:**
[figure not shown]
Study flow of the PREOP-ECHO trial: randomized controlled trial for the intermediate-risk group. Abbreviations. AF, atrial fibrillation; CVA, cerebrovascular accident; ECG, electrocardiography; MET, metabolic equivalent of task; MI, myocardial infarction; NSVT, nonsustained VT; NT-proBNP, N-terminal B-type natriuretic peptide; RVR, rapid ventricular response; TIA, transient ischemic attack; TTE, transthoracic echocardiography; VF, ventricular fibrillation; VT, ventricular tachycardia

**Fig. 2 Fig2:**
[figure not shown]
Study flow of the PREOP-ECHO trial: prospective cohort study for the high-risk group. Abbreviations. AF, atrial fibrillation; CVA, cerebrovascular accident; ECG, electrocardiography; MET, metabolic equivalent of task; MI, myocardial infarction; NSVT, nonsustained VT; NT-proBNP, N-terminal B-type natriuretic peptide; RVR, rapid ventricular response; TIA, transient ischemic attack; TTE, transthoracic echocardiography; VF, ventricular fibrillation; VT, ventricular tachycardia

**Fig. 3 Fig3:**
[figure not shown]
Schedule of enrollment, interventions, and assessments according to the Standard Protocol Items: Recommendations for Interventional Trials (SPIRIT) guideline. Abbreviations. ECG. Electrocardiography; NT-proBNP, N-terminal B-type natriuretic peptide

This multicenter prospective study is an investigator-initiated trial commenced by the Korean Society of Echocardiography. This study is supported by the Korea Health Industry Development Institute (KHIDI) and funded by the Ministry of Health & Welfare, Republic of Korea. The study will be conducted in 22 university hospitals in South Korea from May 2021, with a goal to complete enrollment in 2023.

### Study population

Patients aged 18 to 90 years who are scheduled to undergo elective intermediate- to high-risk noncardiac surgery are eligible for enrollment. According to predefined criteria, participants will be classified into the RCT for the intermediate-risk group or the prospective cohort study for the high-risk group. Patients with current symptoms or signs requiring TTE, patients with a poor functional capacity of less than four metabolic equivalent of task (METs), or patients with a life expectancy of less than 6 months will be excluded. Table 2 provides details on the inclusion and exclusion criteria.

### Randomization and stratification

Informed consent was achieved before screening and enrollment for all participants. Patients in the intermediate-risk group will be randomized to receive echocardiography or not, according to block randomization. An independent organization will generate a random table and assign randomization codes to the subjects using an interactive web response system of the Internet-based Clinical Research and Trial management system (iCReaT, version 2.0). The randomization will be performed on an institutional basis to prevent bias.

Patients in the high-risk group will be enrolled consecutively in the prospective cohort study irrespective of the implementation of preoperative echocardiography or not. The use of TTE is at the discretion of attending physicians. To reduce the risk of selection bias according to age, we will stratify the subjects according to the age of 65 years (Fig. 2).

For both studies, usual postoperative care including drug prescriptions or laboratory examinations can be performed as circumstances demand. Trial discontinuation or modifying allocated intervention can be permitted in case of the participants’ request or the medical need for echocardiography before surgery.

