### Data procurement

Demographic findings, comorbidities, and functional capacity will be prospectively collected before surgery. Electrocardiography, chest X-ray, and laboratory results, including troponin I or T and NT-proBNP levels, will be gathered preoperatively within 90 days before surgery and postoperatively within 3 days after surgery. The samples will be analyzed in the respective institutions. Information on surgery, such as operation time, amount of blood loss and blood transfusion, and anesthetic method, will be collected from operation records after surgery. All data will be anonymized and collected on structured case reporting forms (Additional file 2) and recorded in the iCReaT system provided by the Korea Disease Control and Prevention Agency.

To evaluate the discriminatory predictive power of preoperative echocardiography in the prediction of postoperative CVE compared with clinical risk factors, we will obtain traditional risk indices including Revised Cardiac Risk Index (RCRI) [11], Myocardial Infarction and Cardiac Arrest (MICA) score [10], and American College of Surgeons National Surgical Quality Improvement Program (ACS NSQIP) surgical risk calculator [23].

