### Echocardiography

Transthoracic echocardiographic images and measurements will be obtained at individual hospitals according to guidelines from the American Society of Echocardiography [24]. Left ventricular dimensions are measured in the parasternal long-axis window. LV volumes and ejection fraction are estimated by modified Simpson’s method, and left atrial volume index is measured by the biplane area-length method and adjusted to body surface area. The presence of RWMA is evaluated based on the 17-segment model of the American Heart Association [25]. Indices of diastolic function will be obtained including the peak early diastolic trans-mitral flow velocity (E), the peak late diastolic trans-mitral flow velocity (A), E/A ratio, deceleration time, the early diastolic mitral annular velocity from the septal annulus (e′), E/e′ ratio, maximal velocity of tricuspid regurgitation, and size of inferior vena cava. To detect significant valvular heart disease, conventional or color Doppler interrogation to four cardiac valves will be performed. To measure LV global longitudinal strain, apical 4-, 2-, and 3-chamber images are acquired following the Digital Imaging and Communications in Medicine format and will be analyzed in the core laboratory by a specialist. All echocardiographic parameters obtained will be used in the post hoc analysis for the discovery of the potential predictor of postoperative CVE.

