#### Prospective cohort study for the high-risk group

Baseline characteristics and the endpoints will be analyzed using the same analysis as RCT with correction for confounding variables. Because of the risk of selection bias, the primary endpoint will be analyzed additionally using propensity score matching as a sensitivity analysis.

All endpoints will be analyzed in the full analysis set and tested supplementally in the per-protocol set. The outcomes will be analyzed according to the assigned group, regardless of performing echocardiography or not, for the full analysis set (intention-to-treat analysis). For per-protocol analyses, subjects without endpoints or who violate the study protocol, such as inability to interpret echocardiography due to poor echo window, will be excluded. All individual components composing primary and secondary endpoints occurring within 30 days after index surgery are documented with the date of occurrence. Additional analysis of each individual component will be performed separately using logistic regression. Sensitivity analysis using the Fine-Gray model for the competing risk will be assessed for the competing risk of all-cause death [26].

Statistical analysis will be conducted using SAS (version 9.4, SAS Institute Inc., Cary, NC, USA). Findings with two-sided *p*-values less than 5% will be considered significant. All statistical analyses will be performed by the Biostatistics Collaboration Unit of Yonsei University College of Medicine.

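### In the high-risk cohort, echo predictors and the clinical indices set against them can be assessed together only in patients whom physicians chose to scan, and the planned propensity matching does not cover this

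*Protocol article*

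**What the plan says.** The two studies obtain echo data in different ways (Protocol article, Randomization and stratification). In the RCT, "Patients in the intermediate-risk group will be randomized to receive echocardiography or not, according to block randomization". In the cohort, "Patients in the high-risk group will be enrolled consecutively in the prospective cohort study irrespective of the implementation of preoperative echocardiography or not", and "The use of TTE is at the discretion of attending physicians".

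The echo data have a predictive use as well as a comparative one. Study objectives says that "this trial will develop possible echocardiographic parameters that could be used to determine a preoperative assessment system that would assist in predicting postoperative CVEs", and that the results will inform a Korean guideline. The Background gives prediction of postoperative events as the main purpose. Data procurement collects RCRI, MICA and ACS NSQIP "To evaluate the discriminatory predictive power of preoperative echocardiography in the prediction of postoperative CVE compared with clinical risk factors". The Echocardiography section adds: "All echocardiographic parameters obtained will be used in the post hoc analysis for the discovery of the potential predictor of postoperative CVE".

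Selection bias is named twice. Randomization and stratification says "To reduce the risk of selection bias according to age, we will stratify the subjects according to the age of 65 years". The statistical section for the cohort corrects for confounders and says that "the primary endpoint will be analyzed additionally using propensity score matching as a sensitivity analysis".

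**The concern.** A guideline on preoperative echo has to decide about patients before anyone knows whether they will be scanned. In the cohort, risk by echo finding can be estimated only in the scanned patients, and echo and the clinical indices can be compared head to head only there. If the scanning decision follows age, comorbidity or type of surgery, those patients are not a fair sample of the high-risk population.

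Two quantities are exposed: the absolute event risk attached to a normal or abnormal echo, and the AUC of a clinical index whose spread has been narrowed by the scanning decision.

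Both stated safeguards concern a different contrast. Matching scanned to unscanned patients balances TTE against no TTE. It does not make an analysis run inside the scanned group representative of the cohort. The RCT echo arm has random scanning and is free of this problem, so the two studies could give different prediction results for this reason alone.

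**Working it through.** **Scanned share.** The plan gives no figure for this point, but its cohort sizes suggest the share. Using n per arm = [1.960·√(2p̄(1−p̄)) + 0.842·√(p₁(1−p₁)+p₂(1−p₂))]² / (p₁−p₂)², divided by 0.98 for loss and rounded up:

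- 7% v 3.5%: 637, then 650 per arm, 1,300 in total (stated 1,298).
- 10% v 5%: 435, then 444 per arm, 888 in total (stated 886).

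The stated sizes therefore reproduce as totals of the two age strata with 1:1 scanning, although the text labels them as TTE and no-TTE counts (which would give 1,298/2,184 = 59%). About half scanned is assumed below, i.e. 2,184/2 = 1,092 patients.

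**Illustration 1: scanning driven by a recorded index.** All inputs are assumed: 2,000,000 simulated patients; 8% event rate; logit P(event) = a + 0.8C + 0.4E, with clinical index C and echo score E standardised and correlated 0.3; logit P(scan) = b + gC, with g from 0.7 to 1.5 and half scanned; no action on findings.

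| Quantity | Whole cohort | Scanned only |
|---|---|---|
| Risk, top echo decile | 17.9% | 20.4–21.6% |
| Risk, remaining patients | 6.9% | 8.5–9.7% |
| AUC of clinical index | 0.732 | 0.722–0.700 |

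The inflation of the AUC gain from adding echo was only 0.001–0.004. Weighting by 1/P(scan) recovered the whole-cohort values, with an effective sample of 49–88% of scanned patients.

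**Illustration 2: other scanning patterns.** Assumed: 8.5% event rate; half scanned; 15% abnormal echo; log-odds of the event 0.7 per SD of C, 0.5 per SD of an unrecorded risk U, and 0.7 for an abnormal echo. The results are for scanned patients.

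| Scanning driven by (log-OR per SD) | Risk, abnormal | Risk, normal | Ratio | AUC of C |
|---|---|---|---|---|
| Random (equals whole cohort) | 20.7% | 6.4% | 3.26 | 0.698 |
| C (+1) | 23.7% | 7.9% | 3.00 | 0.684 |
| C (+2) | 24.0% | 8.7% | 2.75 | 0.663 |
| C and U (+1 each) | 23.7% | 8.8% | 2.69 | 0.668 |
| U only (+1) | 22.6% | 7.5% | 3.03 | 0.698 |
| C (−1) | 16.3% | 4.9% | 3.34 | 0.683 |
| C and U (−1 each) | 13.4% | 4.2% | 3.18 | 0.666 |

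The sign of the error in absolute risk follows whom physicians scan. The index AUC falls in either direction when the index drives scanning, and is unchanged when only unrecorded risk does. The abnormal-to-normal ratio shrinks when higher-risk patients are scanned.

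**Action on findings.** Outcome definitions and follow-up lists added drugs, intervention, and delay or cancellation of surgery after an abnormal scan. With scanning on C and U (+1 each), an assumed 30% or 50% risk reduction in scanned abnormal patients gives an abnormal-echo risk of 16.7% or 11.8%. Both lie below the 20.7% of a whole cohort in which nothing is acted on.

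To isolate selection, compare with a whole cohort scanned and managed alike. In a similar model (8.5% before action, g 0.7–1.5, action halving risk), abnormal-echo risk was 9.3% in all against 10.5–11.0% in scanned patients, and index AUC 0.678 against 0.668–0.651. The selection error therefore persists, but it is a separate effect from that of acting on findings.

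**The case against.** A reader might infer that echo risk is overstated and that echo is made to look better than the clinical indices. The documents do not support this, for four reasons.

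- They do not say whom physicians scan. They exclude patients whose symptoms or signs require TTE and those with functional capacity under 4 METs, which removes some obvious routes to risk-driven scanning.
- The distortion of echo's AUC gain (0.001–0.004) is well below its sampling SD of about 0.012 with 1,092 scanned patients. It disappears or reverses once findings are acted on: against a no-action gain of 0.018, scanned patients showed 0.011–0.012 with a 30% risk cut and 0.006 with a 50% cut.
- Where scanning depends on a modelled index and findings are not acted on, the adjusted echo log-odds ratio is unbiased (0.40 estimated, 0.40 true). Predictor associations from the planned multivariable logistic regression would then survive.
- Weighting works in the simulation because scanning there depends on a recorded variable. It cannot undo unrecorded clinical judgement or the effect of acting on findings.

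It is also fair to say that the predictor work is labelled post hoc, that nothing states the two studies will be pooled, and that a condensed article may leave the patient set to a fuller document.

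All of this stands against the stronger reading. The narrower point remains: the article commits all echo parameters to the prediction work, makes prediction a main purpose, and recognises selection bias, yet its stated remedies address only the TTE versus no-TTE contrast.

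**Conclusion.** The point holds in a limited form. Cohort echo data come only from physician-selected patients, and the age strata and propensity matching do not reach the prediction analysis. If scanning depends on clinical risk, absolute risk by echo finding and the clinical indices' discrimination apply to the scanned subset rather than to the high-risk population.

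Under the assumed inputs of the first illustration the error is about 2.5 to 3.7 percentage points in the top echo decile (20.4 − 17.9 to 21.6 − 17.9) and 0.010 to 0.032 in the index AUC (0.732 − 0.722 to 0.732 − 0.700). These sizes rest on the assumed event model and strength of scanning selection, neither of which the documents give. Risk is overstated if higher-risk patients are scanned and understated if lower-risk patients are. No claim about inflated added value of echo follows.

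This is a low-priority improvement. The primary endpoint comparison and the RCT are untouched.

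**What to change.** 1. Report the prediction results separately for the randomised echo arm (unweighted) and for the cohort.
2. Evaluate echo and the clinical indices in the same patients.
3. Describe scanned against unscanned cohort patients on the recorded baseline variables.
4. Add a sensitivity analysis of the cohort prediction results weighted by the inverse probability of being scanned, using the propensity model already needed for the matched analysis.
5. State that weighting removes selection only on recorded variables and does not remove the effect of acting on echo findings.
6. Separately, reconcile the TTE and no-TTE labels on 1,298 and 886 in Sample size calculation with the age-stratum totals that they appear to be.

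The cost is wording and some extra analysis, with no new data. Intervals widen in the weighted analysis: the effective sample is about 50–90% of scanned patients under the assumed inputs, which is why weighting is better placed as a sensitivity analysis than as the main one.
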